## Measures

### Childbirth-related post-traumatic stress symptoms

#### Diaries

For each CB-IM, participants will be asked to write in a diary the time it occurred, its content and to report, from 0 = *not at all* to 10 = *extremely*: (1) how distressing it was, (2) to what extent they had the impression that the memory was happening here and now (*nowness*^43^) and (3) its sensorial modalities. CB-IM will be defined to participants as ‘*involuntary memories of the labour or childbirth that come to mind without warning. They can be vivid and emotional, and are often like a mental image, such as a photograph or film. They can involve all the senses (…). They can be very short, elusive and fragmented’.*^27^ Participants will use electronic diaries hosted in REDCap, or a paper version (eg, if not able to use the electronic ones), adapted from previous work.^27^

#### City Birth Trauma Scale (CBTS)

This questionnaire assesses CB-PTSS during the past week, and diagnostic criteria of PTSD according to the DSM-5.^44^ Twenty-two items, using a 4-point Likert scale, assess the four CB-PTSS clusters (*re-experiencing*, *avoidance*, *negative cognitions and mood*, *hyperarousal*). Original instructions of the CBTS will be adapted for participants who had multiple childbirth(s) to complete the questionnaire regarding the index traumatic childbirth. Good psychometric properties were found for the French version of the CBTS.^45^

### Anxiety and depression symptoms

#### Anxiety subscale of the Hospital Anxiety and Depression Scale (HADS-A)

This subscale assesses anxiety symptoms and consists of seven items using 4-point Likert scales.^46^ Good psychometric properties are reported for the French version of the HADS.^47^

#### Edinburgh Postnatal Depression Scale (EPDS)

This 10-item questionnaire measures postnatal depression symptoms during the past week with 4-point Likert scales.^48^ The French version of the EPDS has good psychometric properties.^49^

### Intervention-related measures

#### Intervention acceptability

Participants will answer the Feedback questionnaire III assessing intervention acceptability, usefulness, and expectations regarding its effects. These questions, based on previous work,^27^ have been designed to best match the intervention characteristics.

#### Heart rate variability

Participants’ HRV will be recorded using a Firstbeat Bodyguard 2 (Firstbeat Technologies, Jyväskylä, Finland) ECG device during the whole intervention procedures. Count aloud tasks A and B will measure HRV baseline and recovery, in order to compare participants HRV during Narrative tasks A and B, and Tetris gameplay.

#### Subjective distress

Visual analogue scales will be presented to participants at 11 timepoints during the intervention to assess their subjective distress level from 0 = *not stressed and/or anxious at all* to 10 = *extremely stressed and/or anxious*.

### Sociodemographic and obstetric characteristics

#### Sociodemographic variables

A sociodemographic questionnaire will assess participants’ age, nationality, marital status, education level and trauma history.

#### Obstetric and medical data

Obstetric and medical data will be extracted from participants’ medical record, such as childbirth mode, gestational age and Apgar scores. Birth-related information will also be collected at baseline, through a self-report questionnaire (eg, presence of a relative, perceived threat for self or infant).

### Other variables

This study includes other outcomes, aiming to specify the effects of the intervention, presented in table 2.

**Table 2 T2:** Other trial outcomes, including instruments and time points

Variables	Instruments	Timepoints	Description
Cognitive flexibility	Cognitive flexibility scale^50^	T1	Cognitive flexibility defines, inter alia, the capacity to adapt to the situation and being flexible.^50^
Cue specificity	Feedback questionnaires I and III	T2/T4, T7	These questionnaires will assess the similarity between childbirth narration and the original childbirth memory.
Context specificity	Feedback questionnaires II and III	T3/T5, T7	Questions will assess the similarity between the intervention context and the original traumatic context.
Diary compliance	Diaries	T1, T3, T5, T6	Diary compliance will check the extent to which participants were able/remembered to report their CB-IM at the end of each diary.
HRV control variables	Questionnaire on HRV control variables	T1, T2/T4	This questionnaire will contain control variables regarding the analyses of the HRV (eg, weight, height, medicine use, cigarettes and alcohol consumption).
Video games use	Feedback questionnaires I and III	T2/T4, T7	Questions will assess participants’ video games use (eg, engagement in the game during the intervention, Tetris perceived difficulty, video games habits, and Tetris use postintervention).
Sleep	Sleep questionnaire	T3/T5	This questionnaire will evaluate the number of hours of sleep during the 24 hours following the intervention.
Concurrent psychological treatment	Feedback questionnaire III	T7	A question will check the absence of a concurrent psychological treatment in relation to the index childbirth during study participation.

CB-IM, childbirth-related intrusive memories; HRV, heart rate variability; T1, weeks 1 and 2 preimmediate intervention; T2, day 15; T3, weeks 1 and 2 postimmediate intervention; T4, day 30; T5, weeks 1 and 2 postdelayed intervention; T6, weeks 5 and 6 postimmediate intervention; T7, feedback phone call.

### Sample size calculation

A sample size calculation was conducted for our primary and secondary outcomes based on the results obtained from the pilot study,^27^ assessing the efficacy of the same intervention using a single-group pre–post design, and from laboratory studies using RCT designs to assess the efficacy of a similar BI-VT.^23 24^ A sample size of 90 participants (45 allocated in each group) is estimated to be necessary to detect the effect of the intervention on our primary and secondary outcomes with an 80% power (α = 0.05). Based on our experience with this study population,^11 27^ a conservative estimate of a 30% drop-out and exclusion was assumed. We therefore plan to recruit 120 participants in total.

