During a phone call, the study coordinator (DF) will screen interested mothers. The presence and number of CB-IM over the past 2 weeks will be assessed with the item B1 of the Clinician-administered PTSD scale for Diagnostic and Statistical Manual of Mental Disorders, Fifth Edition, (DSM-5),^40^ and the T-ACE will be used to assess alcohol consumption.^41^ Eligible mothers who signed the consent form will be randomly allocated to the IIG or WCG with a 1:1 ratio. To ensure concealment, a scientific collaborator not involved in data collection created a block randomisation list stratified by centre, which will be automatically generated by the Research Electronic Data Capture (REDCap) software. To limit waitlist condition-related bias on participants’ self-reports,^32 33^ participants will be blind to group allocation. To that matter, participants will only be informed that both groups will complete the same assessments and receive the intervention, but in a different order. For an overview of study procedures for both groups, see figure 1. To improve completion of study assessments, the study coordinator will follow participants’ progression during the whole study and participants will receive reminders to complete questionnaires.

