### Secondary outcomes

Secondary outcomes will be:

The change in CB-PTSS between: (a) baseline and at 2 weeks postimmediate intervention across groups, (b) baseline and follow-up in the IIG.The change in the number of CB-IM between baseline and follow-up in the IIG.The acceptability of the intervention in both groups.

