### Data management and statistical analysis

Participants’ entries in electronic diaries and questionnaires will be directly stored in the REDCap software. The research staff will enter manually the rest of the data collected during the screening, the intervention and paper diaries in REDCap. All data will be hosted on a high security server of the Lausanne University Hospital performing automatic continuous backups. All primary outcome data and a random 5% of the rest of the data will be double-checked. Independent and blind coders will inspect diary entries to detect any non-compliance with instructions and count the number of CB-IM. A blind statistician will perform the analyses. To ensure blinding of the coders and the statisticians, they will receive a dataset not indicating which allocation group corresponds to the IIG or WCG. Only the study team will have access to the full coded trial dataset.

For primary outcomes, group differences regarding change of the number of CB-IM between baseline and the 2 weeks postimmediate intervention will be analysed using repeated-measures analyses (intention-to-treat analyses). For the secondary outcomes, repeated-measures analyses will be performed to analyse group differences concerning CB-PTSS between baseline and at 2 weeks postimmediate intervention. Logistic regression analyses will also compare the proportion of participants meeting the diagnostic criteria for CB-PTSD across time and groups. Furthermore, repeated measures analyses will serve to analyse change in the number of CB-IM and CB-PTSS between baseline and follow-up in the IIG. Group differences regarding the proportion of participants meeting the diagnostic criteria for CB-PTSD will be analysed with logistic regression analyses. The mean score of the intervention acceptability will be calculated across both groups. Additional post-hoc analyses conducted will be described as such in publications. Missing data will be dealt with using multiple imputation procedures, if appropriate.

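### The 80% power statement covers all secondary outcomes, but only one of the four listed is a 45-versus-45 comparison, and 80% power is not shown for the added CB-PTSD diagnosis analysis

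*Protocol article*

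**What the plan says.** The protocol article, under Sample size calculation, gives one figure for all outcomes: "A sample size of 90 participants (45 allocated in each group) is estimated to be necessary" to detect the intervention's effect "on our primary and secondary outcomes with an 80% power", at α = 0.05. It states that "A sample size calculation was conducted for our primary and secondary outcomes based on the results obtained from the pilot study" and from laboratory randomised studies. It prints no effect size, standard deviation or event rate for any outcome. It assumes 30% drop-out and exclusion and sets recruitment at 120. Participants are "randomly allocated to the IIG or WCG with a 1:1 ratio".

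Under Secondary outcomes there are four items, counting the two parts of the first separately:

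- the CB-PTSS change from baseline to 2 weeks, between groups;
- the CB-PTSS change from baseline to follow-up, immediate intervention group (IIG) only;
- "The change in the number of CB-IM between baseline and follow-up in the IIG";
- acceptability, both groups.

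Under Study procedures (T6), the waitlist group (WCG) has no follow-up assessment. Under Data management and statistical analysis, the only plan for acceptability is this: "The mean score of the intervention acceptability will be calculated across both groups". The same section adds a binary analysis that is not on the outcome list: "Logistic regression analyses will also compare the proportion of participants meeting the diagnostic criteria for CB-PTSD across time and groups".

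**The concern.** A power figure belongs to a particular test of a particular hypothesis. The protocol attaches one figure, from one two-group sample size, to outcomes that differ in kind: one between-group comparison, two uncontrolled within-group changes and one descriptive mean. A binary diagnosis analysis is placed alongside them, and a binary outcome usually needs more participants than the score behind it.

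What is at stake is interpretation. A non-significant CB-PTSD comparison could be taken as the result of a test with 80% power. A fall in symptoms at 6 weeks in the IIG could be reported as a powered effect of the intervention, although natural recovery is not controlled for. Regression to the mean is not controlled for either, and women enter on a minimum of four CB-IM in 2 weeks.

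**Working it through.** **Inputs from the protocol.** α = 0.05 (sidedness not stated; two-sided assumed), power 80%, 45 per group, 1:1 allocation, 30% loss, 120 recruited. Effect sizes and diagnosis rates are not given.

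**1. The plan's own figure.** With no effect size printed, 90 cannot be reproduced forwards. Solving backwards for a two-group comparison of means:

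d = (1.960 + 0.842) × √(2/45) = 0.591, or 0.597 with the t-test.

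Check: n = 2 × 2.802² / 0.591² = 45 per group. So 90 corresponds to a standardised difference of about 0.60. This is the review's inference, not a sponsor assumption. A one-sided test would give 0.524.

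**2. Matching the claim to the outcomes.**

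| Item | Data used | Does 80% power from 45 v 45 apply? |
|---|---|---|
| CB-PTSS to 2 weeks | both groups | Yes |
| CB-PTSS to follow-up | IIG only | No control, so it tests change over time, not an intervention effect |
| CB-IM to follow-up | IIG only | As above |
| Acceptability | pooled mean | No hypothesis to power |
| CB-PTSD diagnosis (analysis section only) | binary, time and groups | Not shown; see step 4 |

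**3. IIG-only changes as paired tests.** With 45 pairs, 80% power needs dz = 0.43. A pre-post change of 0.597 SD gives dz = 0.597 / √(2(1 − r)). Power is 79% at correlation r = 0, 91% at 0.3 and 97% at 0.5. These tests are not short of power; what they lack is a comparator.

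**4. CB-PTSD diagnosis.** Assume a normal symptom score, one cut-off and a shift of d = 0.597. With control proportion pC, the treated proportion is pT = 1 − Φ(z(1 − pC) + d). Power is Φ((pC − pT − 1.960 × SE0) / SE1), with SE0 from the pooled proportion, SE1 unpooled, and 45 per group.

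| pC | pT | Power |
|---|---|---|
| 0.10 | 0.030 | 27% |
| 0.20 | 0.075 | 40% |
| 0.30 | 0.131 | 50% |
| 0.50 | 0.275 | 59% |
| 0.62 (best) | 0.385 | 61% |
| 0.80 | 0.597 | 56% |

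Worked at the best threshold: difference 0.2347, SE0 = 0.1054, SE1 = 0.1025, so Φ((0.2347 − 0.2066) / 0.1025) = Φ(0.27) = 61%. Cross-check using the efficiency of a median split, 2/π: Φ(2.802 × √(2/π) − 1.960) = Φ(0.28) = 61%. At the best threshold 71 to 72 per group would be needed for 80%.

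**5. Sensitivity of the best case to the assumed effect.**

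- True d of 0.5, 0.7 and 0.8: 47%, 75% and 85%.
- 0.591 read in SD units of change, with pre-post correlation 0.3, 0.5 and 0.7: 74%, 60% and 40%.
- 0.591 read as a baseline-adjusted effect, same correlations: 56%, 48% and 35%.

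**6. The protocol's own attrition.** 120 × 0.70 = 84, or 42 per group. For any two-group effect that 90 detects with 80% power, power at 84 is Φ(2.802 × √(42/45) − 1.960) = Φ(0.75) = 77%. This step needs no effect size. Keeping 90 after 30% loss would take 90 / 0.70 = 128.6, that is 129.

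**The case against.** The strongest reply is that the blanket phrase is loose editing, and that the diagnosis figure is built on inputs the article does not contain. Much of this stands.

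- A reader might infer that 61% is a ceiling on power for CB-PTSD. The documents do not support that. The calculation is said to cover several outcomes; if another outcome set the 90, the assumed CB-PTSS effect could be larger, and at d = 0.8 the best case is 85%. The article also describes the diagnosis as DSM-5 criteria on the CBTS, not a total-score cut-off, and plans a logistic regression over time and groups. Step 4 is a simplification of that.
- A reader might infer that the IIG-only outcomes are underpowered. They are not, as step 3 shows. The protocol is also open that they are changes within one group and explains why the WCG has no follow-up.
- A reader might take 0.60 as the sponsor's assumption. It is only what 45 per group implies under a t-test, and CB-IM is a count that may have been sized in another way.
- Diagnosis is not among the four listed outcomes, so it is not strictly inside the sample size sentence.

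What the reply does not meet is the mismatch itself. The sentence claims 80% power to detect the intervention's effect on the secondary outcomes, and three of the four listed items cannot bear that claim. This is stated in the article, not left to an unseen analysis plan.

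**Conclusion.** The point holds as a minor correction of wording. Without any assumption: one of four listed secondary outcomes is a 45-versus-45 comparison, two are uncontrolled, and one has no hypothesis. With only the protocol's own 30% loss, and a two-sided two-group comparison of means, power for an effect that 90 detects with 80% falls to about 77% at 84 participants.

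Conditionally: if 90 was set by the smallest detectable CBTS difference, and diagnosis behaves like a cut of a normal score, the diagnosis comparison has about 27% to 50% power at 10% to 30% control prevalence and about 61% at best. The supportable statement is that 80% power has not been shown for this analysis, not that it is known to be absent. None of this says that the primary comparison is badly sized.

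**What to change.** Replace the single power sentence with one that:

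- limits the 80% statement to the between-group comparisons of change from baseline to 2 weeks in CB-IM and in the CBTS score;
- gives, for each, the effect size, its scale and the sidedness that the sponsor actually used (the back-solved 0.60 should not be written in as the sponsor's figure);
- states that 30% loss from 120 leaves 84, with about 77% power at the effect that set the 90;
- claims no power for acceptability;
- describes the IIG-only follow-up changes as uncontrolled within-group changes;
- names the CB-PTSD proportion as supportive of the CBTS score comparison, reported with a 95% confidence interval.

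The cost is wording only. No participants or assessments are added, and the stated power becomes narrower and slightly less favourable.

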**Methods and analysis:**

In this multicentre, single-blind, randomised controlled trial being undertaken at one regional and one university hospital in Switzerland, 60 participants will be allocated to the Immediate Intervention Group (IIG), receiving the immediate intervention on day 15, and 60 participants to the WCG receiving the delayed intervention on day 30. All participants will report their CB-IM during the 2 weeks preimmediate and postimmediate intervention in diaries. The IIG will additionally report their CB-IM over weeks 5 and 6 postimmediate intervention. Self-report questionnaires will assess CB-PTSS at 2 weeks preimmediate and postimmediate intervention in both groups, and at 6 weeks postimmediate intervention in the IIG. A feedback questionnaire will evaluate the intervention acceptability. The primary outcome will be group differences in the number of CB-IM between the 2 weeks preimmediate and postimmediate intervention. Secondary outcomes will be CB-PTSS at 2 and 6 weeks postimmediate intervention, the number of CB-IM at weeks 5 and 6 postimmediate intervention, and intervention acceptability.

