### Population, recruitment, group allocation and blinding

Mothers with a minimum age of 18 years, who gave birth at least 6 weeks prior to the screening in one of the two study centres (one university hospital, being the main study centre, and one regional hospital from Switzerland), and suffer from CB-IM will be eligible to participate. To avoid a floor effect regarding CB-IM reduction, we will only include mothers reporting at least four CB-IM over the 2 weeks prior to the screening. Exclusion criteria will be insufficient French-speaking level to complete the assessments, established intellectual disability or psychotic illness, an ongoing psychological treatment in relation to childbirth, propranolol medication (due to suspected effects on memory reconsolidation^39^), alcohol and/or illicit drug abuse, being pregnant, perinatal loss of a child born during the index traumatic childbirth (ie, the childbirth triggering the CB-IM targeted during the intervention) or a life-threatening illness of the mother or infant(s). Moreover, mothers not able to distinguish potential IM related to another traumatic event from CB-IM linked to the index traumatic childbirth will be excluded. Importantly, data related to any participants that reported less than two CB-IM at baseline will be excluded from relevant analyses to avoid a floor effect, or if they stated having a concurrent psychological treatment in relation to childbirth during study participation.

Adverts will be displayed in nurseries and practices of midwives, gynaecologists and paediatricians. Study information will also be shared on social media. In addition, study centres will send a text message to invite potentially eligible mothers who gave birth in their hospitals to participate in the study.

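### The sample-size figures do not fit together: 120 recruited with 30% loss leaves 84 evaluable participants, not the 90 stated as needed for 80% power

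*Protocol article*

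**What the plan says.** The Sample size calculation section of the protocol article gives three figures in sequence.

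- Number needed: "A sample size of 90 participants (45 allocated in each group) is estimated to be necessary" to detect the intervention effect on the primary and secondary outcomes, at 80% power and α = 0.05.
- Expected loss and target: "a conservative estimate of a 30% drop-out and exclusion was assumed. We therefore plan to recruit 120 participants in total".

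The abstract allocates 60 participants to each group, and the section on population, recruitment, group allocation and blinding says participants are "randomly allocated to the IIG or WCG with a 1:1 ratio". So 120 is the number randomised. That section also describes part of the expected loss: "data related to any participants that reported less than two CB-IM at baseline will be excluded from relevant analyses". The same rule applies to participants who report concurrent psychological treatment related to the childbirth.

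The section on data management and statistical analysis labels the primary analysis intention-to-treat and allows multiple imputation where appropriate.

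**The concern.** The wording presents 120 as the result of taking 90 and allowing for a 30% loss. A loss of 30% is a share of those recruited, so the target should be the number needed divided by the share retained. 120 falls short of that result, so the number needed, the loss rate and the target cannot all be right.

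At stake is whether a reader can rely on the justification printed for the trial's size. As written, it implies that the trial keeps its planned power with 30% of participants lost. On its own inputs it does so only up to a 25% loss.

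**Working it through.** **Inputs, all from the Sample size calculation section unless noted**

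- Evaluable number needed, n: 90 (45 per group)
- Loss fraction, L: 0.30
- Recruitment target, R: 120 (60 per group in the abstract; 1:1 allocation)
- Power 80%, α = 0.05; whether the test is one- or two-sided is not stated
- Effect size: not printed

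**Step 1. Try to reproduce 120**

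- Standard inflation, R = n/(1 − L): 90/0.70 = 128.6, so 129. Per group, 45/0.70 = 64.3, so 65, giving 130. This does not reproduce 120.
- Adding 30% to the number needed, R = n × (1 + L): 90 × 1.30 = 117. This is near 120 but not equal to it.
- Standard inflation with L = 0.25: 90/0.75 = 120 exactly.

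The target therefore matches a 25% loss exactly, or a 30% add-on approximately. It does not match a 30% loss.

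**Step 2. What 120 delivers at the stated loss**

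- 120 × (1 − 0.30) = 84, or 42 per group
- Shortfall: 90 − 84 = 6 participants
- Largest loss that still leaves 90: 1 − 90/120 = 25%

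**Step 3. Effect on power**

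The number 90 cannot be re-derived without an effect size, so the standardised effect d is back-solved from 45 per group at 80% power. Power is then recomputed at 42 per group. This assumes a simple two-group comparison; the planned repeated-measures analysis may behave somewhat differently.

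| Assumption | d implied by 45 per group | Power at 42 per group |
|---|---|---|
| t-test, two-sided 5% | 0.597 | 77.2% |
| Normal approximation, two-sided 5%: d = (1.960 + 0.842) × √(2/45) | 0.591 | 77.2% |
| t-test, one-sided 5% | 0.528 | 77.5% |
| t-test, two-sided, if 45 was rounded up from just above 44 | 0.604 | 78.1% |

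The range is about 77–78%. On the two-sided t-test, the effect detectable with 80% power moves from 0.60 to 0.62 SD.

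**Step 4. Which outcomes are affected**

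One total of 90 is given for the primary and secondary outcomes together. On the same two-sided t-test, an outcome with at least 82.7% power at 45 per group still has at least 80% at 42 per group. Only an outcome whose own requirement is at or close to 90 drops below 80%.

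**The case against.** The arithmetic itself is hard to contest, since nothing elsewhere in the article reconciles the three figures. The objections concern what follows from it.

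- **Intention-to-treat and imputation.** The primary analysis is labelled intention-to-treat, and missing data may be imputed, so some drop-outs could stay in. The 30% is not tied to a time point either, and the primary comparison ends before the delayed intervention, the follow-up and the feedback call, so part of the loss could come later. This stands in part. But the 30% also covers exclusions; imputation does not bring back participants removed by rule, and it does not restore information that was never collected. The calculation itself inflates for the full 30%.
- **30% is described as conservative.** Actual loss may be lower, and 120 is enough up to 25%. That is a reason to print 25% as the loss the target covers. It does not make 120 follow from 30%.
- **One total for several outcomes.** A reader might infer that the primary outcome, or every between-group outcome, falls below 80% power. The article does not support that. It does not say which outcome drives the 90, and the others may have power to spare.
- **Outcomes assessed only in the immediate intervention group.** A reader might also infer that these are weakened because they would rest on about 42 women. That is not shown. They are within-group changes, and for the same standardised effect (0.597, applied to change scores) a paired test on 42 women has about 97% power; it has 80% power down to about 0.44.
- **Cause of the slip.** Multiplying by 1.30 is a plausible explanation, but it gives 117. The article does not show how 120 was reached, and the point does not depend on it.

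**Conclusion.** The point holds as an internal inconsistency in the Sample size calculation section. With 120 recruited and 30% lost, 84 remain rather than 90; a 30% loss calls for 129 (130 with equal groups), and 120 is right only for a loss of at most 25%. This needs no assumption beyond the printed figures.

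The effect on power is smaller and conditional. For an outcome that needs exactly 90, power would be about 77–78% instead of 80%, assuming a two-group t-test at α = 0.05 and that all of the 30% is lost to the analysis. It would be misread as a finding that the primary outcome is underpowered: no effect size is printed, and outcomes that need fewer participants may still reach 80%. The absence of an effect size, or of a separate number for the outcomes of the immediate intervention group alone, is no fault here, since a condensed article may leave those to the full protocol.

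Six participants and under three points of power make this a minor to moderate correction. The inconsistency does not bear on bias, type I error or the choice of outcome.

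**What to change.** Keep 120 and correct the sentence in one of two ways:

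1. State that 120 recruited yields 90 evaluable participants if drop-out and exclusion together are at most 25% (90/0.75 = 120); or
2. Keep the 30% assumption and state that 84 evaluable participants (42 per group) are expected, with about 77–78% power for the outcome that needs 90.

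For the second option, the sponsor should replace the back-solved range with the power from its own effect size and planned analysis.

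Either change costs one sentence and no extra participants; the second also means printing a slightly less favourable power figure. If the sponsor wants both a 30% allowance and 90 evaluable, the target becomes 129, or 130 with equal groups, which is 9 or 10 more participants. A shortfall of this size does not by itself call for that.
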